#### Evaluations of Aims

##### Tests of Hypotheses

All analyses will use intent-to-treat using all randomized participants. All assumptions will be tested. If the normality assumption is violated, the nonparametric Mann-Whitney *U* test will be used.

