##### Testing of Aim 1: Feasibility and Acceptability of NiteCAPP CARES and NiteCAPP SHARES

The feasibility and acceptability of NiteCAPP CARES and NiteCAPP SHARES will be evaluated using average completion rates (number of sessions completed), adherence (measured through sleep diaries and logs), and satisfaction and utility ratings. These variables will be compared for NiteCAPP CARES and NiteCAPP SHARES using independent samples 2-tailed *t* tests.

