##### Testing of Aims 2 to 4: Primary and Mechanistic and Secondary Outcomes

A mediated GEE model [58] (clusters are individuals measured over 4 time points) will test causal paths between intervention effects on the primary and secondary outcomes (Figure 3). On the basis of a priori hypotheses, separate GEE models, including group (NiteCAPP CARES and NiteCAPP SHARES), time (baseline, after treatment, and 6-month and 12-month follow-ups), and their interaction as predictors, will be conducted for each primary CG outcome (aim 2: insomnia severity, sleep onset latency, wake after sleep onset, sleep efficiency, arousal, and inflammation), secondary CG outcome (aim 3: health, mood, burden, and cognitive performance), and secondary outcome for persons with dementia (aim 4: actigraphy total wake time for persons with dementia). Potential covariates affecting the mechanistic outcomes (Table 2) or technology use by CGs and persons with dementia (eg, Internet Intervention Utility Questionnaire [38]) will be assessed and used as covariates if significant.

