### Missing Values

The SAS PROC GEE weighted model handles missing data completely at random or at random. When measures are collected over time, some participants may not complete the study. Unlike repeated measures ANOVA, which excludes them from analysis, weighted GEE retains them (increasing power and producing unbiased estimates).

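### The Mann-Whitney fallback is not limited to Aim 1, so as written it can displace the group-by-time GEE for Aims 2 to 4

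*Protocol article*

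**What the plan says.** All from the Protocol article:

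- **Tests of Hypotheses** stands ahead of the aim-by-aim sections. It commits that "All analyses will use intent-to-treat using all randomized participants", adds that "All assumptions will be tested", and then gives the fallback: "If the normality assumption is violated, the nonparametric Mann-Whitney" U test will be used. No aim, outcome or model is named.
- **Testing of Aim 1** follows directly: "These variables will be compared for NiteCAPP CARES and NiteCAPP SHARES using independent samples 2-tailed" t tests.
- **Testing of Aims 2 to 4** plans "separate GEE models, including group (NiteCAPP CARES and NiteCAPP SHARES), time" and the interaction, the full time factor being "time (baseline, after treatment, and 6-month and 12-month follow-ups), and their interaction as predictors". The primary caregiver outcomes are listed as "insomnia severity, sleep onset latency, wake after sleep onset, sleep efficiency, arousal, and inflammation".
- **Missing Values** gives the reason for the model when participants do not complete: "weighted GEE retains them (increasing power and producing unbiased estimates".
- **Power Analysis** expects 15% to 20% dropout and takes 80 as the powered sample.

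**The concern.** The fallback suits a two-sample t test. It does not suit a repeated-measures model. If the rule is followed for Aims 2 to 4, three things go wrong.

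1. The planned hypothesis, a difference between arms in the course over four time points, is no longer the one tested.
2. The dropout weighting that the Missing Values section relies on disappears, and the analysis shrinks to those seen at one visit. Differential attrition is a limitation that the article itself names under Strengths and Limitations.
3. The main analysis of each outcome is settled by a preliminary test on the trial data, so outcomes in the same family could end up with different analyses and different effect measures.

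The reason for switching is also weak. GEE inference with a robust variance rests on the mean model and on independent clusters, not on normally distributed outcomes.

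**Working it through.** **1. The passages side by side.**

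| Feature | GEE planned for Aims 2 to 4 | Mann-Whitney U |
|---|---|---|
| Data per person | up to four time points | one value |
| Group-by-time interaction | yes | none |
| Covariates | allowed | none |
| Weighting for dropout | yes | none |
| Participants used | retains non-completers | those with that value observed |
| Needs normal outcomes | no, with robust variance | no |

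The last row gives no reason to move from the left column to the right.

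**2. Participants at stake.** Number left out = recruited × dropout.

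- 120 (Power Analysis): 120 × 0.15 = 18; 120 × 0.20 = 24.
- 100 (Trial Design and Study Setting): 100 × 0.15 = 15; 100 × 0.20 = 20.

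These apply at a visit by which all the expected dropout has occurred. Earlier visits lose fewer.

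**3. How often the switch could occur.** The article gives no distributions, so this is illustrative. With 40 per arm (80 split equally, an assumption), a Shapiro-Wilk test at 5% rejected normality in essentially 100% of simulated log-normal trials and in about 5% of normal ones. An outcome of log-normal shape would therefore nearly always be switched.

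**4. Type I error when only completers are used.** Assumptions: no true effect; 50 per arm; baseline-to-post correlation 0.5, as in the Power Analysis; dropout probability 0.4 × baseline rank in one arm and 0.4 × (1 − rank) in the other, averaging 20%; nominal 5%; 3,000 runs.

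| Analysis of completers | Log-normal | Normal |
|---|---|---|
| Mann-Whitney, post-treatment value | 9.3% | 8.8% |
| Raw change score | 7.9% | 10.1% |
| Baseline-adjusted regression (log scale for log-normal data) | 4.3% | 5.4% |

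The inflation comes from ignoring baseline-dependent dropout, not from using ranks: the unweighted change score is inflated too. Weighted GEE was not simulated. The baseline-adjusted regression stands in for a method that is valid under this mechanism.

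**5. Power, and why it is not part of the point.** Assumptions: post-treatment visit, 40 per arm, effect 0.5 SD, two-sided 5%, correlation 0.5.

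Analytic, normal data: power = Φ(0.5/s × √(n/2) − 1.96).

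- Single-visit comparison: s = 1, n = 40, Φ(2.236 − 1.96) = 61%.
- Mann-Whitney, efficiency 0.955: n = 38.2, Φ(2.185 − 1.96) = 59%.
- Change from baseline: s = √(2(1 − 0.5)) = 1, again 61%.
- Baseline-adjusted: s = √(1 − 0.5²) = 0.866, Φ(2.582 − 1.96) = 73%.

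Simulated, log-normal data, effect on the log scale:

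| Log SD, correlation | Mann-Whitney, post | Mann-Whitney, change | Raw change contrast | Baseline-adjusted, log scale |
|---|---|---|---|---|
| 0.6, 0.5 | 57% | 48% | 43% | 70% |
| 0.6, 0.6 | 59% | 57% | 50% | 78% |
| 0.7, 0.5 | 56% | not run | 39% | 71% |
| 1.0, 0.5 | 56% | 43% | 30% | not run |

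With complete data, the post-treatment contrast of a group, time and interaction model equals the difference in mean change. The raw change column is therefore the right stand-in for the model as written, and Mann-Whitney has more power than it in every row.

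**The case against.** The strongest reply is that the sentence was never meant for Aims 2 to 4. The phrase about all analyses belongs to the intent-to-treat sentence. The t test in the next section is the only planned test that both assumes normality and has Mann-Whitney as its direct counterpart. The GEE section provides a model for every outcome with no exception, and Missing Values likewise allows none. Read so, the passages agree. This may well be the intention, and it is why the point is one of scope and not proof that the GEE will be abandoned. But the sentence sits in the section that governs every aim and carries no limit, so an analyst following the text could apply it to any outcome.

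Three stronger readings are tempting, and the documents do not support them.

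- *The fallback loses power.* The 70% and 78% figures show what a baseline-adjusted log-scale analysis would gain, and the article does not plan that analysis. Against a raw change contrast, Mann-Whitney gains power on skewed data and loses almost nothing on normal data (59% against 61%).
- *Most primary outcomes are skewed.* No distributions are given. Right skew is plausible for sleep onset latency, wake after sleep onset, spectral heart rate variability power, CRP and IL-6. Nothing suggests it for the Insomnia Severity Index or the summed stress scales.
- *Baseline is discarded.* The article does not say whether raw or change values would be ranked. Ranked change would use baseline, though still without the interaction or the weighting.

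Transforms and links are often left to an analysis plan, and their absence is not the complaint. The complaint is a rule that this article does fix, and fixes too broadly.

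**Conclusion.** The point holds as a matter of scope and should be fixed. As written, the fallback reaches Aims 2 to 4. There it conflicts with the planned group-by-time test, with the weighted handling of dropout and with the commitment to analyse everyone randomized, and it makes the choice of main analysis depend on the data. These conclusions rest on the text and on what the two methods can do, not on simulation.

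The size depends on assumptions. Up to 18 to 24 of 120 participants, or 15 to 20 of 100, could fall out of a single-visit test. Type I error near 9% was seen under one assumed mechanism with opposite baseline dependence in the two arms; if dropout were unrelated to arm and baseline, this inflation would not be expected. How many outcomes would be switched is unknown, because their distributions are not given. No claim of lost power against the planned model is made.

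**What to change.** - Limit the Mann-Whitney sentence to the Aim 1 comparisons, for example by moving it into that section.
- For Aims 2 to 4, state that the weighted GEE with robust standard errors is the analysis for every outcome, whatever a normality test shows.
- Prespecify a log transform or log link for the plausibly skewed outcomes: sleep onset latency, wake after sleep onset, spectral heart rate variability power, CRP and IL-6.
- Keep any rank-based analysis as a sensitivity check only.

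The cost is a change of wording, best made before unblinded data are analysed. Effects on the log scale are reported as ratios and need a little more explanation. A log transform also needs a stated rule for zero values, which a log link avoids. If the authors meant the sentence only for Aim 1, nothing in their intended fallback changes.

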##### Testing of Aim 1: Feasibility and Acceptability of NiteCAPP CARES and NiteCAPP SHARES

The feasibility and acceptability of NiteCAPP CARES and NiteCAPP SHARES will be evaluated using average completion rates (number of sessions completed), adherence (measured through sleep diaries and logs), and satisfaction and utility ratings. These variables will be compared for NiteCAPP CARES and NiteCAPP SHARES using independent samples 2-tailed *t* tests.

##### Testing of Aims 2 to 4: Primary and Mechanistic and Secondary Outcomes

A mediated GEE model [58] (clusters are individuals measured over 4 time points) will test causal paths between intervention effects on the primary and secondary outcomes (Figure 3). On the basis of a priori hypotheses, separate GEE models, including group (NiteCAPP CARES and NiteCAPP SHARES), time (baseline, after treatment, and 6-month and 12-month follow-ups), and their interaction as predictors, will be conducted for each primary CG outcome (aim 2: insomnia severity, sleep onset latency, wake after sleep onset, sleep efficiency, arousal, and inflammation), secondary CG outcome (aim 3: health, mood, burden, and cognitive performance), and secondary outcome for persons with dementia (aim 4: actigraphy total wake time for persons with dementia). Potential covariates affecting the mechanistic outcomes (Table 2) or technology use by CGs and persons with dementia (eg, Internet Intervention Utility Questionnaire [38]) will be assessed and used as covariates if significant.

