**Conclusions:**

This randomized controlled trial tests NiteCAPP CARES, a web-based CBT-I for rural caregivers. The knowledge obtained will address not only what outcomes improve but also how and why they improve and for how long, which will help us to modify NiteCAPP CARES to optimize treatment potency and support future pragmatic testing and dissemination.

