## Methods

### Trial Design and Study Setting

Dyads (n=100) consisting of CGs with chronic insomnia and their coresiding persons with dementia will be recruited from Columbia and surrounding areas in Missouri, United States, and randomized to 4 sessions of NiteCAPP CARES or NiteCAPP SHARES. The groups will receive bimonthly boosters. Baseline and posttreatment assessments as well as 6-month and 12-month follow-ups will measure sleep, arousal, biomarkers of inflammation and neurodegeneration, health, mood, burden, and cognition.

Graduate therapists and assessors will obtain written informed consent from CGs and persons with dementia, if possible. If the person with dementia is unable to consent (determined by consultation with the first author [[name]]), a legally authorized representative must sign a consent form on their behalf. If the person with dementia becomes unable to provide consent during the course of the study, the legally authorized representative will be asked to reconsent on behalf of the care recipient. Dyads in both groups will receive US $125 at baseline, US $150 after treatment, US $175 at 6-month follow-up, and US $200 at 12-month follow-up, as well as treatment at no cost. NiteCAPP SHARES participants will be offered NiteCAPP CARES at no cost after the study.

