**3. Coping and stress management and cognitive therapy**
Sleep prescription for caregiver and person with dementia will be updated as appropriate. Coping and stress management techniques will be taught. Caregiver and person with dementia will be taught how to identify maladaptive thoughts and replace them with balanced thoughts.

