### Analytical Approach

#### Power Analysis

Power will be simulated using SAS 9.4 statistical software (SAS Institute Inc) using a generalized estimating equations (GEE) design (clusters are individuals measured over 4 time points) with an autoregressive working correlation structure (correlation decreases as time point distance increases, *ρ*=0.5, 1 million Monte Carlo integrations simulated) [57]. The approach described by Schluchter [58] will fit GEE models with and without mediator to estimate mediated effect (exploratory aim). Sample size of 80 is powered (>.80) to detect small to large Cohen *d* mediation effects. Given an anticipated dropout rate of 15% to 20%, we will recruit a total sample of 120.

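### The mediated GEE is said to test causal paths, but comparing models with and without the mediator relies on a non-randomised association and cannot establish one

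*Protocol article*

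**What the plan says.** Under Testing of Aims 2 to 4, the protocol article states that a mediated GEE "will test causal paths between intervention effects on the primary and secondary outcomes". The primary outcomes there are sleep, arousal and inflammation; the caregiver secondary outcomes are health, mood, burden and cognitive performance. The sentence carries no exploratory label.

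The Power Analysis section cites the same method reference and says that the approach "will fit GEE models with and without mediator to estimate mediated effect (exploratory aim"). Testing of Exploratory Aim also places mediators under the exploratory aim.

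The Figure 3 legend adds paths from posttreatment to 6 months and from 6 to 12 months; the figure itself is not shown. The only covariate rule, under Testing of Aims 2 to 4, concerns variables affecting the mechanistic outcomes or technology use, and keeps them if significant. Randomization and Blinding describes allocation of arm only.

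The Abstract's conclusions say that the knowledge obtained "will address not only what outcomes improve but also how and why they improve and for how long", and the closing Conclusions section makes a similar statement.

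**The concern.** Randomisation protects the path from arm to mediator. It does not protect the path from mediator to outcome, because nobody is randomised to a level of sleep or arousal. Several mediators and outcomes are self-reports by the same caregiver at the same assessment: insomnia severity and perceived stress on one side, depression, anxiety and burden on the other. Caregiving events or general distress can move both. The covariate rule is not aimed at such common causes, and no data can test for the unmeasured ones.

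At stake is the mechanistic conclusion. If CARES improves sleep as hypothesised, the analysis may credit sleep with changes in mood or burden that it did not cause. The trial's findings are meant to guide modification of the program, so a wrong mechanism could misdirect that work.

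**Working it through.** **The plan's own figure.** The protocol states: "Sample size of 80 is powered (>.80) to detect small to large Cohen" *d* mediation effects. It gives no values for the two paths, so the power figure cannot be reproduced. I take N=80 from it, together with the four visits ("clusters are individuals measured over 4 time points") and the autoregressive correlation of 0.5. Inflating 80 for 20% dropout gives 80/(1 − 0.20) = 100, the number of dyads under Trial Design. The 120 in Power Analysis does not follow, but that is a separate matter.

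**What the contrast estimates.** Let *c* be the group effect on the outcome without the mediator in the model and *c′* the effect with it. With an identity link, and up to the weighting by the working correlation,

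*c* − *c′* = *a* × β,

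where *a* is the arm effect on the mediator and β is the within-arm regression of outcome on mediator. If the mediator has no causal effect but shares causes with the outcome, then in standardised units β = ρ, their correlation, and the contrast is *a*ρ:

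- *a* = 0.5, ρ = 0.3: 0.5 × 0.3 = 0.15 (simulated mean 0.151)
- *a* = 0.8, ρ = 0.3: 0.8 × 0.3 = 0.24 (simulated mean 0.238)

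**How often a test of it rejects.** Not in the document and therefore assumed: *a* of 0.5 to 0.8 SD, ρ = 0.3, 1:1 allocation and two-sided alpha 0.05. The simulation uses the group-by-posttreatment coefficient from GEE fits with and without the mediator, and a *z* test of the difference with a joint robust variance. The causal effect of the mediator is set to zero. Rejection at N=80 under three separate codings of this set-up:

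| Coding | Same-visit mediator | Lagged mediator, baseline values adjusted |
|---|---|---|
| 1 | 49% to 90% | 13% to 26% |
| 2 | 61% to 96% | 5% to 8% |
| 3 | 58% to 94% | 7% to 19% |

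With 1,000 runs the Monte Carlo standard error is at most √(0.25/1000) = 1.6 percentage points. The spread between rows therefore comes mainly from set-up details, and only rounded ranges should be quoted.

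**Conditions and sensitivity** (coding 2, N=80):

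- ρ = 0: rejection 0.0% to 4.5% for *a* from 0 to 1.0, so the test does not over-reject.
- *a* = 0: at most about 6%.
- Same visit, *a* of 0.5 to 0.8: 45% to 84% at ρ = 0.2, and 66% to 97% at ρ = 0.5.
- Same visit, ρ = 0.3, with baseline mediator and outcome added: 83% to 99%. Baseline adjustment alone does not cure the problem.

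**When the outcome really improves by another route.** With a direct CARES effect of 0.6 SD on the outcome (coding 3), the over-rejection remains. In 47% to 72% of trials a significant improvement and a false mediated effect occur together.

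**The case against.** The strongest reply is that the plan already treats mediation as exploratory. Power Analysis and Testing of Exploratory Aim both say so, no rule in the document declares a causal mediator, and Aims 2 to 4 also have separate group-by-time models. This stands in part: it limits the damage, but it does not make the causal wording correct, and the sentence under Testing of Aims 2 to 4 carries no such label.

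A reader might infer that the plan will usually declare a false mechanism and has almost no protection against one. The documents do not support that. The high rates need a same-visit mediator and outcome, and the interval wording in the Figure 3 legend is compatible with lagged paths, for which the rates are far lower. The exact test statistic is also a construction from a brief description, and the effect and correlation are assumed. Objective measures such as heart rate variability, hair cortisol, cognitive performance tests and blood biomarkers may share fewer causes with reported sleep than questionnaires do.

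A reader might also infer that the CARES content itself produces false mediation, since in session 3 "Coping and stress management techniques will be taught". It does not do so alone. Arm is in both models, so a direct effect on mood or burden goes into the group coefficient; a within-arm association is still needed. The Introduction also lists stress management among the techniques meant to engage sleep and arousal.

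Finally, confounder sets and sensitivity analyses are often left to an analysis plan. Their absence from the article is not the point here. The point is a stated causal property that the described method lacks.

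**Conclusion.** The concern holds in a limited form. The described method estimates a product of one randomised and one observational quantity, so a significant mediated effect is compatible with mediation but does not establish a causal path. This follows from the algebra and needs no assumed numbers.

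The size of the error does depend on assumptions. At N=80, with an arm effect on the mediator of 0.5 to 0.8 SD and a same-visit correlation of 0.3 from shared causes, false rejection is about 50% to 95% for same-visit measures. It is about 5% to 25% for a lagged mediator with baseline adjustment. Which form applies cannot be settled without Figure 3. Lagging reduces the problem without removing it, because a shared cause can persist between visits. The randomised group-by-time comparisons, and hence the evidence on what improves, are not affected.

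**What to change.** 1. Under Testing of Aims 2 to 4, label the mediated GEE exploratory, in line with Power Analysis and Testing of Exploratory Aim. Replace the claim to test causal paths with a statement that the model estimates associations consistent with mediation.
2. Include baseline mediator and baseline outcome in the models both with and without the mediator. This addresses confounding carried by baseline levels only and should not be presented as sufficient.
3. Report the residual mediator-outcome correlation at which each mediated effect loses significance.
4. Limit the statements on how and why outcomes improve, in the Abstract and in the closing Conclusions, to what this analysis supports.

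Lagged paths may be reported alongside, but not as removing the confounding.

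The cost is a more modest mechanistic claim and a little extra analysis of data already planned. Sample size, assessments and the randomised comparisons do not change.

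### The group-by-time GEE for Aims 2 to 4 leaves the baseline group difference free, so its interaction terms are change-from-baseline contrasts: valid, but less efficient than a baseline-adjusted comparison

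*Protocol article*

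**What the plan says.** The section on testing Aims 2 to 4 fixes one model form for every primary and secondary outcome: "separate GEE models, including group (NiteCAPP CARES and NiteCAPP SHARES), time (baseline, after treatment, and 6-month and 12-month follow-ups), and their interaction as predictors". Baseline is therefore a level of time, not a covariate. Other covariates, those thought to affect the mechanistic outcomes or technology use, "will be assessed and used as covariates if significant". The outcome's own baseline value is not named, and the shown text does not set the two arms to a common baseline mean. The section does not say which contrast from the model is the test.

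The baseline values will be available. Under Trial Design and Study Setting, "Baseline and posttreatment assessments as well as 6-month and 12-month follow-ups will measure sleep, arousal" and the other outcome domains, and Table 2 schedules the outcome measures at all four assessments.

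The Power Analysis assumes a GEE "with an autoregressive working correlation structure (correlation decreases as time point distance increases", with ρ = 0.5. It states: "Sample size of 80 is powered (>.80) to detect small to large Cohen *d* mediation effects". It gives no alpha and no single effect size.

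**The concern.** A model with group, four-level time and their interaction spends a parameter on the baseline difference between arms, a quantity known to be zero in expectation. The interaction terms then subtract the baseline difference with a coefficient of 1, whatever the correlation between baseline and follow-up. When that correlation is below 0.5, subtracting baseline is noisier than ignoring it. Under an autoregressive pattern the correlation with baseline falls as visits get later, so the interaction terms are weakest at 6 and 12 months. Those visits carry the question of how long any benefit lasts, which the Conclusions present as a main contribution of the trial. With about 80 dyads expected to be analysed, a maintained effect could be missed for a reason that costs almost nothing to remove.

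**Working it through.** **Plan's own figure.** Power above 0.80 at N = 80 refers to mediation effects described only as small to large. Without alpha, a value of d or the mediation paths, it cannot be reproduced. The check below concerns the plain group contrasts.

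**What the interaction estimates.** With complete data the model is saturated in group and time. The group coefficient is the baseline difference between arms, and each interaction coefficient is the difference at that visit minus the difference at baseline. A GEE with autoregressive working correlation, fitted to simulated complete data, gave exactly these values.

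**Whether the covariate rule repairs it.** Suppose the baseline value b entered this same model with coefficient γ. The adjusted difference at visit t is D(t) − γD(b), and at baseline D(0) − γD(b). The interaction is their difference, D(t) − D(0), so γ cancels and nothing is gained.

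**Inputs.**
- From the Power Analysis: N = 80, and autoregressive ρ = 0.5. With visits treated as equally spaced, the correlation r with baseline is 0.5 after treatment, 0.5² = 0.25 at 6 months and 0.5³ = 0.125 at 12 months.
- Assumed, because not stated for these aims: 1:1 allocation (40 per arm), two-sided alpha 0.05, equal variances at all visits (SD 1), and d = 0.5 for illustration.

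**Formulas.** Variance per participant: V = 2(1 − r) for the change contrast and V = 1 − r² with baseline adjustment. SE = √(2V/40). Power = Φ(d/SE − 1.96).

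| Visit | r | V, change | V, adjusted | Ratio | Power, change | Power, adjusted | Loss (points) |
|---|---|---|---|---|---|---|---|
| After treatment | 0.5 | 1.00 | 0.75 | 1.33 | 0.609 | 0.733 | 12.4 |
| 6 months | 0.25 | 1.50 | 0.9375 | 1.60 | 0.447 | 0.637 | 19.0 |
| 12 months | 0.125 | 1.75 | 0.984 | 1.78 | 0.394 | 0.616 | 22.2 |

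The ratios need no effect size and no alpha; the power columns need both. At both follow-ups the change contrast has a larger variance (1.50 and 1.75) than a comparison that ignores baseline (1.00). The effect detectable with 80% power would fall from 0.63 to 0.54, from 0.77 to 0.61 and from 0.83 to 0.62.

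**Sensitivity, 40 per arm (after treatment / 6 months / 12 months).**
- d = 0.2: loss of 3.4 / 4.1 / 4.5 points.
- d = 0.4: 11.0 / 14.6 / 16.6.
- d = 0.6: 10.7 / 20.0 / 24.4.
- d = 0.8: 3.8 / 12.7 / 17.8.
- d = 0.5 with a higher baseline-outcome correlation: about 6 points at r = 0.7 (V 0.60 against 0.51) and 2 points at r = 0.8 (V 0.40 against 0.36).
- d = 0.5, baseline SD assumed to be 0.7 of the follow-up SD, as entry screening might cause: change-contrast power 0.71 / 0.55 / 0.50, a loss of about 2 / 8 / 12 points.

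**If another contrast is tested.** The same fitted model also yields the plain difference between arms at each visit (group plus interaction). Its V is 1.00, so its power at d = 0.5 is 0.609 at every visit. Against 0.733, 0.637 and 0.616, the loss is about 12, 3 and 1 points.

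**The case against.** The strongest reply is that the planned model is a standard one and gives unbiased estimates under randomisation. That stands: this is a loss of efficiency, not an error, and no part of the article contradicts another here.

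The second reply is that the tested contrast is not named. The Objectives ask for effects at each post-treatment visit, and the plain visit difference from the same model would lose little at 6 and 12 months. That also stands, and it limits the larger figures to the interaction terms. It does not remove the point: the model is built around the interaction, and even the plain difference loses about 12 points after treatment in the illustration. A statistical analysis plan that is not shown may name the contrast, and Figure 3, also not shown, has a baseline node. Neither alters the model as the text states it.

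The third reply is that ρ = 0.5 is an input to a power simulation, not a measured correlation for each outcome, and that the visits are unequally spaced. That is correct, and the sizes are conditional on it.

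A reader might also infer that the baseline diary week, because it is also the entry screen (Eligibility Criteria and Screening), makes imbalance between arms likely. The documents do not support that. The screen applies equally to both arms. It can produce regression to the mean in both, but it does not make a chance difference between them more likely.

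**Conclusion.** The point holds as a matter of efficiency. The stated model leaves a baseline difference free that randomisation sets to zero in expectation, and neither the covariate rule nor any other shown text supplies the missing adjustment. Under the article's simulation correlation, with equal spacing and equal variances, the interaction contrasts carry 1.33, 1.60 and 1.78 times the variance of baseline-adjusted ones.

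A reader might turn this into a flat loss of 12 to 22 points of power under the plan's own correlation. The documents do not support that: the figure also needs d = 0.5, alpha 0.05 and 40 per arm, and the first two are nowhere stated for these aims. The defensible statement is a loss of about 3 to 24 points for the single-visit interaction contrasts over d = 0.2 to 0.8 at N = 80. It shrinks further with high baseline-outcome correlation, a narrower baseline spread, or a test of the plain visit difference. The planned analysis would not be invalid or biased for this reason. The change is still worth making, because the data are already collected.

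**What to change.** In the section on testing Aims 2 to 4, keep baseline as a response in the weighted GEE but remove the group effect at baseline, so that both arms share one baseline mean. Name the group difference at each of the three post-baseline visits as the prespecified contrast. This form keeps all randomised dyads, in line with the intent-to-treat statement under Tests of Hypotheses and the aim of retaining non-completers under Missing Values.

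An alternative is to model only the three post-baseline visits, with group, time, group-by-time, the outcome's own baseline value and baseline-by-time. The baseline value should enter by prespecification, not by a significance test.

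Run the power simulation under whichever model is chosen.

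The cost is a sentence or two of analysis text and a rerun of the simulation, with no new data or participants. There are small downsides. The common-baseline form reaches full efficiency only if the working correlation is about right, so that structure should be stated for the analysis as well as for the simulation. The covariate form omits dyads with no post-baseline data, which matters with 15% to 20% dropout expected, and it needs a rule for missing baseline values.
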